#### Administrative data

Area-level administrative data for general practices will be matched via postcodes within a geographical area defined by the practice catchment using publicly available mapping files [56]. These mapping files are updated regularly by practices, which will enable us to account for changes in practice catchments over time (e.g. due to practices merging or a change in catchment population). All data required are drawn from publicly available sources.

We will use the same sampling approach as described above, but all potential “exposed” and “unexposed” practices will be included, and not just those that are recruiting survey participants. For our initial analyses, general practices in the area of the route that is not proceeding as planned will not be treated separately as the data we are using in the first wave pre-dates the cancellation announcement for the first wave. For subsequent waves, we will treat the general practices from these regions separately from those in areas where the HS2 route is proceeding as planned. We will include a sample of general practices from other areas of England as a second “control” group.

### Analysis plans

We will pre-register an analysis protocol for each wave of data collection, for each data source (cohort surveys, interviews and focus groups, and administrative data) on the Open Science Framework (DOI 10.17605/OSF.IO/HQGDT).

#### Cohort data

To examine the impact of HS2 on outcomes over time, we will use difference-in-differences (DiD) analysis [57]. This quasi-experimental design compares outcomes between groups over time to assess the impact of a policy or environmental intervention. It is an established approach for analysing data from natural experiments where exposure to the intervention is outside control of the researcher, as is the case with the HS2 development [58,59]. The main impact analysis will be conducted separately for Phase 2a, Phase 2b, and the part of the route not proceeding as planned. We will estimate the overall intervention effect and investigate the differences across key subgroups, such as age or housing status, via exploratory subgroup analyses. We will use appropriate univariable and multivariable models, depending on the outcome, and will adjust for baseline characteristics and sampling.

We will explore the impact of exposure in two different ways: area-based and individually computed distance [60]. Our primary analyses will use the area-based definition to enable comparison between individuals living in unexposed areas and individuals living in the exposed areas, which will necessarily treat all individuals as equally exposed. However, as proximity to the HS2 route is likely to be an important factor for mental health and wellbeing outcomes, for our secondary analyses we will focus on those living in exposed areas and define exposure using individually computed distance from the route i.e. creating a gradient of exposure.

We considered the sample sizes needed for 90% power based on a 0.05 significance level for a two-sided test. All calculations were conducted using Stata version 15.0. We examined this for our three main analytical approaches:

**Cross-sectional (within-wave) primary outcome analyses:** Data from 2011 estimated the mean WEMWBS for adults in England as 51.6 (standard deviation 8.7) [61,62]. Based on this, a sample size of 178 per group (356 in total for each HS2 Phase) is required to detect a minimally important difference of 3 points in the WEMWBS between intervention (n = 178) and control (n = 178) groups. Our target sample sizes far exceed this.**Longitudinal (across-wave) primary outcome analyses:** The DiD approach used for the main analysis is a test of an interaction, rather than the test of main effect (simple difference in means); sample size requirements for tests of interactions are four times those required to test a main effect of the same size [63]. Therefore, 356 responses would be needed from both intervention and control cohorts at each of two time points for the same power from this analysis framework. As the recruitment target is 1,200 participants per group per HS2 Phase (n = 4,800 in total), and 600 participants per group for the part of the route not proceeding as planned (1,200 in total) the study will be well-powered to detect a meaningful difference in the primary outcome using a DiD framework, and separate analyses for Phases 2a and 2b will be feasible.**Longitudinal subgroup analyses:** Differential impacts of HS2 on particular groups in the population will be approached analytically as a “triple difference” (difference in difference in difference) analysis (a three-way interaction). It would require a further fourfold increase in sample size for a differential impact of the same size as the main effect meaning an overall sample size of 5,696 would be required (or possibly greater if the groups being compared are not of equal size). Using all three waves of data collection or combining both Phase 2a and Phase 2b sites we would achieve this sample size. However, we will not have sufficient power to undertake subgroup analyses for the section of the route which is not proceeding as planned.

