## Design

### Aim

The overarching aim of this research is to investigate the extent to which individuals and communities exposed to the planning, construction and operation of HS2 experience positive or negative mental health and wellbeing impacts, focused specifically on anxiety, depression, and general wellbeing. It will address the following research questions:

What are the positive and negative mental health and wellbeing impacts of HS2?Do these impacts change over time and what explains them?Are impacts felt differently across groups within a community?What are the health economic implications of the mental health and wellbeing impacts of HS2?

Due to changes to the HS2 development plan, particularly regarding the Phase 2b East route, the scope of the project was changed during the planning stage to encompass the impacts that may occur when changes are made late in the planning stage. This means that the geographical scope of the study is based on the planned HS2 route as of June 2021 i.e. all parts of the Phase 2a and Phase 2b route shown in Fig 1, even those no longer going ahead as planned.

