### Limitations

As discussed in the Introduction, the planning stage of HS2 began in 2009/2010, while this research began in 2021; this means that the study cannot capture a true “baseline” measure of mental health and wellbeing in communities along the route of HS2. Our analysis of administrative data partially mitigates this, but cannot provide the level of detail on mental health and wellbeing that would have been captured by a survey, interviews, or focus groups.

Defining exposure to the HS2 development is not straightforward. While we set a 5km boundary around the Phase 2 HS2 route to define our exposed group (and this is larger than the HS2 homeowner compensation scheme boundary), it is possible that the impact of HS2 extends beyond this. To mitigate this, the interviews with local stakeholders may offer insight into the impacts of HS2 on a larger geographic area which can be used to inform our overall conclusions from the study. In addition, it is still possible participants that we have defined as “unexposed” may be affected by HS2 through impacts on other aspects of their lives such as commuting or place of work. However, our sampling approach is designed to minimise this risk and reduce contamination between the two groups. Additionally, while we are intending to focus on Phase 2 of the HS2 development, those living at the southern end of the Phase 2 route will also have had some exposure to Phase 1 of the development, which is now at the construction stage. Although Phase 1 is not within the scope of this research project, we will be able to try to explore this potential effect using information on the geographical proximity of participants to both HS2 phases.

Recruiting and retaining study participants is likely to be challenging given the length of time of the study. There is likely to be participant drop-out; to mitigate this, we will recruit new participants at wave 2 and 3 to ensure we maintain a sufficient sample sizegeneral. This approach has been used in long-term studies of infrastructure project health impacts to manage participant attrition [48]. Our use of general practices to recruit people will mean that people who are not registered with a GP will be excluded from the research, although the GP registration in England is almost universal.

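### The main cohort difference-in-differences is presented as the intervention effect, but with wave 1 about 13 years into planning it estimates only the change in the exposed-unexposed gap since wave 1

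*Protocol article*

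**What the plan says.** The Cohort data part of Analysis plans opens with "To examine the impact of HS2 on outcomes over time, we will use difference-in-differences (DiD) analysis". It continues: "The main impact analysis will be conducted separately for Phase 2a, Phase 2b, and the part of the route not proceeding as planned", and then "We will estimate the overall intervention effect"; the same sentence goes on to exploratory comparisons between subgroups. The sample size text that follows confirms the status of this analysis: "The DiD approach used for the main analysis is a test of an interaction". It sizes the analysis for two time points.

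The Aim section asks to what extent "individuals and communities exposed to the planning, construction and operation of HS2 experience positive or negative mental health and wellbeing impacts". The logic model, described under Overview and framework, has planning, construction and operation each able to act on mental health by its own mechanisms. The same section says that the three waves were originally meant to line up with those three stages.

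On timing, Limitations states "the planning stage of HS2 began in 2009/2010, while this research began in 2021; this means that the study cannot capture a true “baseline” measure". Status and timeline dates the first survey mailing to 18 May 2023. Limitations offers the administrative data as a partial mitigation.

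The Cohort data text also plans a within-wave comparison of exposed and unexposed groups on the primary outcome. It is listed first of the three principal approaches for which sample size was considered.

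**The concern.** A DiD returns the effect of an intervention when its first time point precedes the intervention. Here the first time point is, by the article's own definition of exposure, well inside it. The effect of planning that has built up by wave 1 is part of what the study sets out to measure, yet the main analysis subtracts it.

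Two results could then mislead. A harm that stays constant from planning into construction gives a DiD of zero. A harm that eases but persists gives a positive DiD, which looks like a benefit. The Health economic analysis section repeats the same DiD for care costs and EQ-5D-5L utility and then scales the result by duration and population, so a constant effect would enter those totals as zero.

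**Working it through.** **The plan's own figures.** Inputs from the Cohort data text: SD 8.7, difference 3 points, two-sided 0.05, power 90%.
- Per group: 2 × (1.960 + 1.282)² × 8.7² / 3² = 177 by the normal approximation, and 178 with the t distribution. The article gives 178.
- DiD: 2 × 178 = 356 per group per time point. The article gives 356. The SE there is 8.7 × √(4/356) = 0.922 and the power for 3 points is 90.2%.

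The sample size arithmetic is sound. The issue is what the DiD estimates.

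**Timing.** From the start of 2010 to 18 May 2023 is 13.4 years. Counting from mid-2009 it is 13.9, and from mid-2010 it is 12.9.

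**What each contrast estimates.** Let B be any stable difference between exposed and unexposed areas that HS2 did not cause. Let E1 and E2 be the HS2 effects at wave 1 and at a later wave. Assume parallel trends otherwise.
- Gap at wave 1 = B + E1
- Gap at the later wave = B + E2
- DiD = (B + E2) − (B + E1) = E2 − E1

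The DiD removes B, which is its strength, and removes E1 with it. The within-wave gap keeps the effect to date but also keeps B. The DiD equals E2 only if E1 = 0, meaning that planning had no effect by May 2023.

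**Size.** The documents give no value for E1 or E2, so the gaps below are assumptions (WEMWBS points, exposed minus unexposed, B = 0). SE of DiD = 8.7 × √(4/n): 0.502 at n = 1,200 per cell (the target for Phase 2a and for Phase 2b) and 0.710 at n = 600 (the target for the part not proceeding).

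| Wave 1 gap | Later gap | DiD | Significant result, n = 1,200 | n = 600 |
|---|---|---|---|---|
| 0 | −3 | −3 | harm, over 99.9% | harm, 98.8% |
| −1.5 | −3 | −1.5 | harm, 84.8% | harm, 56.0% |
| −3 | −3 | 0 | 2.5% in each direction | 2.5% in each direction |
| −3 | −1.5 | +1.5 | apparent benefit, 84.8% | apparent benefit, 56.0% |
| −3 | −1 | +2 | apparent benefit, 97.8% | apparent benefit, 80.4% |
| −3 | 0 | +3 | apparent benefit, about 100% | apparent benefit, 98.8% |

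In rows 3 to 5 exposed residents are still worse off at the later wave. For comparison, the within-wave contrast at 1,200 per group has SE 8.7 × √(2/1200) = 0.355 and 98.8% power for a 1.5-point gap.

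These percentages treat responses as independent. Clustering by practice and the return of the same people across waves would change the SEs and rejection rates, but not the DiD column.

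**The case against.** A reader might infer that the article claims a total effect accumulated since 2009. The text does not support that. In its full sentence, overall stands against the subgroup analyses, and the paragraph begins by describing impact over time. What remains is narrower: the result is still called the effect of an intervention that the article defines to include planning.

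A reader might also infer that a null DiD would be reported as no impact, so that RQ1 would be answered wrongly. That does not follow either. The within-wave contrast is a planned primary-outcome analysis and would show a persisting gap. Table 1 maps RQ1 to qualitative and administrative data as well, and the triangulation section joins the sources for each research question. The administrative series includes practices active from 2013. It still starts after planning began, however, and contains no WEMWBS.

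Three further points deserve weight:
- The missing baseline is disclosed. The disclosure sits in Limitations and does not reach the description of the main analysis.
- Change between stages is a legitimate target and is close to what RQ2 asks. That supports naming it as such.
- DiD is a defensible main choice because it removes stable area differences. The within-wave gap does not, and Limitations warns that people with stronger feelings about HS2 may be more likely to take part. This is why the gap should not replace the DiD.

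Finally, analysis protocols will be pre-registered for each wave and data source. Detailed estimand wording may belong there, but the article already fixes the label and the method, and the two do not match.

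**Conclusion.** The point holds in a limited form. On the article's own dates and definition of exposure, the cohort DiD for Phases 2a and 2b estimates the change in the exposed-unexposed gap since wave 1, not the effect of HS2. This applies to outcomes first measured in the wave 1 survey, above all WEMWBS. A constant effect gives zero, and a harm that eases but persists gives an apparent benefit. The article concedes the lack of a baseline without carrying it into what the DiD is said to estimate, and it does not say how the DiD and the within-wave contrast are to be read together when they differ.

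The cancellation is exact and needs no assumption about size. How much it matters depends on the wave 1 effect, which the documents do not give. If that effect is nil, the DiD is unaffected. If it is 3 points, the whole minimally important difference used for the sample size is lost from the estimate. The rejection rates are illustrations under SD 8.7, independent responses and assumed gaps.

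**What to change.** In the Cohort data analysis text and in the wave-specific analysis protocols:
1. Replace the intervention-effect label with a definition of the DiD as the change in the exposed-unexposed gap since wave 1, when the route was already in planning.
2. Report the adjusted exposed-unexposed gap at each wave, including wave 1, beside the DiD for every phase. Add the caveat that the gap may include pre-existing area differences and self-selection.
3. State that a null DiD is not evidence of no impact, and that a positive DiD may be recovery from a planning-stage effect.
4. Do not make the cross-sectional gap the sole estimate for RQ1.

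The cost is wording. Both contrasts are already planned and no new data are needed. The downside is that the main estimate will support a narrower conclusion than the present label suggests.

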#### Cohort data

The primary outcome will be mental wellbeing as measured by the Warwick-Edinburgh Mental Wellbeing Scale (WEMWBS). The WEMWBS scoring range is 14–70. As it approximates a normal distribution it is designed to be analysed using parametric approaches. The minimally important level of change is between 3 and 8 points [41,42]. We will analyse the following secondary mental health outcomes, most of which will also be included in the analysis of administrative data:

Anxiety and depression incidence. This will be measured via a review of general practice notes using the general practice Quality and Outcomes Framework (QOF; https://digital.nhs.uk/data-and-information/data-tools-and-services/data-services/general-practice-data-hub/quality-outcomes-framework-qof) Systematized Nomenclature of Medicine (SNOMED) Clinical Terms codelists;Use of community-provided psychological therapy services. This will be measured using data from the Improving Access to Psychological Therapies national data set (IAPT; https://digital.nhs.uk/data-and-information/data-collections-and-data-sets/data-sets/improving-access-to-psychological-therapies-data-set);Prescribing of antidepressants and anxiolytics. This will be via review of general practice prescribing records;Prevalence of long-term mental health problems. This will be measured via a question from the GP Practice Survey (GPPS; https://gp-patient.co.uk/) that will be included in the study survey.

Other potential secondary outcomes include alcohol use, and social support (measured via survey questions). We will also collect health and social care service utilisation data (primary and secondary care, personal social services, medications) for the health economic analysis.

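### The effect near the route is not estimated against unexposed residents: the controlled cohort analysis ignores distance, and the distance analysis focuses on exposed residents

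*Protocol article*

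**What the plan says.** The cohort part of the Analysis plans (Protocol article) describes two ways of handling exposure.

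- **Primary.** A difference-in-differences (DiD) comparison of exposed with unexposed areas, "which will necessarily treat all individuals as equally exposed".
- **Secondary.** Having said that proximity probably matters for mental health and wellbeing, the plan continues: "for our secondary analyses we will focus on those living in exposed areas and define exposure using individually computed distance from the route", giving a gradient of exposure.

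The Exposure definition section sets the boundary at 5km. It notes that this is much wider than the homeowner compensation area (under 1km) and says the width is deliberate, so that wider effects on greenspace and roads are captured. The subgroups named as examples are age and housing status; distance is not among them. The sections on cohort sampling and sample size do not stratify by distance.

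The power statement applies one effect size to the whole exposed group: 178 per group "is required to detect a minimally important difference of 3 points in the WEMWBS between intervention (n = 178) and control (n = 178) groups". For the DiD, "356 responses would be needed from both intervention and control cohorts at each of two time points". The targets are 1,200 per group per Phase, and 600 per group for the part of the route not proceeding as planned.

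**The concern.** Each of the two analyses lacks what the other has. The area-based DiD has a control group but averages over everyone within 5km. The distance analysis separates near from far but sets the control group aside. As stated, no cohort analysis asks how wellbeing changed close to the route relative to unexposed residents.

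This matters because a within-exposed gradient is a purely relative measure. Any effect common to the whole 5km zone cancels out of it. The gradient can show that near residents fared differently from far residents, but not whether near residents were harmed or helped relative to no exposure, or by how much. The plan's own reason for choosing 5km, that effects may spread widely, is also the reason why residents at 1 to 5km may be a contaminated reference. Research questions 1 and 3 (what the impacts are, and whether groups differ) would both be served by a controlled near-route estimate.

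**Working it through.** **Inputs from the protocol.** SD 8.7; difference of 3 points; two-sided 0.05; 90% power; 1,200 or 600 per group per wave; exposed zone 0 to 5km.

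**Assumptions, not in the protocol.** The share f of exposed respondents living within 1km (varied; 20% corresponds to even density over 0 to 5km); the shape of the effect; independent waves unless stated; no clustering by practice. Power = Φ(d/SE − 1.96), plus a negligible opposite tail.

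**The plan's own figures.** The two-sample calculation gives 177 per group by the normal approximation and 178 by the noncentral t (power 90.05%). For the DiD, SE = 8.7·√(4/n); n = 356 gives SE 0.922 and power 90.2%. Both stated figures reproduce.

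**What the area DiD can detect.** At n = 1,200, SE = 8.7·√(4/1,200) = 0.502, so 90% power needs an average effect of (1.96 + 1.2816)·0.502 = 1.63 points over everyone within 5km. At n = 600, SE = 0.710 and the figure is 2.30 points. If 3 points are confined to a near-route share f, the average is 3f. So f must be about 54% for 90% power and 47% for 80% (77% and 66% at 600 per group).

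**Step effect: 3 points within 1km, none beyond; f = 20%, n = 1,200.**
- Area DiD: effect 0.6, SE 0.502, power 22%.
- Linear gradient among exposed: slope 0.576 per km, SE = √2·8.7/√(1,200·25/12) = 0.246, power 65%.
- Near versus unexposed: SE = 8.7·√(2/240 + 2/1,200) = 0.870, power 93%.
- Near versus rest of exposed: SE = 8.7·√(2/240 + 2/960) = 0.888, power 92%.

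Varying the share and the sample size:

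| n per group | f | Area DiD | Linear gradient | Near v unexposed |
|---|---|---|---|---|
| 1,200 | 10% | 9% | 30% | 72% |
| 1,200 | 20% | 22% | 65% | 93% |
| 1,200 | 30% | 43% | 84% | 98% |
| 1,200 | 50% | 85% | 94% | 99.8% |
| 600 | 20% | 13% | 38% | 68% |

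**Exponential decay: 3·exp(−km/2), even density, n = 1,200.**
- Mean over 0 to 5km: 6·(1 − e^−2.5)/5 = 1.10. Area DiD power 59%.
- Mean within 1km: 6·(1 − e^−0.5) = 2.36. Near versus unexposed, power 77%.
- Mean over 1 to 5km: 6·(e^−0.5 − e^−2.5)/4 = 0.79. Near versus far therefore estimates 2.36 − 0.79 = 1.57, one third below the true near-route effect, with power 43%.
- Linear gradient: power 53%.

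The shortfall of 0.79 points is bias relative to the unexposed reference, so a larger sample does not remove it.

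**Linear decline from 3 to 0 over 5km, n = 1,200.** The average is 1.5 points. Area DiD power is 85% and gradient power 68% (slope 0.6 per km). The decline averages 2.7 within 1km and 1.2 over 1 to 5km, so near versus far gives 1.5 of 2.7.

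**Sensitivity to within-person correlation.** At an assumed 0.5, every SE falls by √2. In the step case with f = 20% and n = 1,200, power becomes 39% (area), 91% (gradient) and 99.8% (near versus unexposed).

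**The case against.** A reader might infer that a near-route effect is likely to be missed altogether. The documents do not support that. It needs a small near-route share, which the protocol does not give, and an effect concentrated close to the line. With a smooth linear decline the area DiD has 85% power. The gradient may also pick up a concentrated effect, particularly if the same people respond at each wave, as the plan intends. The lowest figures also use the bottom of the plan's own range ("The minimally important level of change is between 3 and 8 points"): 5 points confined to under 1km would give the linear gradient 97% power even with independent waves. In the step case the unexposed reference adds almost nothing to power (93% against 92% for near versus rest of exposed), and the plan does not commit the gradient to a straight line. All of this stands, and it limits the claim about detection.

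It also stands that the 5km average is a deliberate and legitimate estimand. It matches the population within 5km used for extrapolation in the Health economic analysis, and its simplification is openly stated. The 1km line is a compensation boundary, and the protocol does not present it as the limit of the effect.

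Two further arguments carry less weight. First, per-wave analysis protocols are still to be pre-registered, so model detail may sit there. But the article already states the population of the distance analysis, so the point addresses a stated choice rather than missing detail. Second, the area average and the slope together could imply a near-route effect. That works only under an assumed shape, which data already planned could replace with a direct estimate.

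**Conclusion.** The concern holds in a limited form. As written, the cohort plan gives no estimate of the near-route effect against an unexposed reference. The within-exposed gradient gives only near-versus-far differences, and these understate the near-route effect whenever residents further out but within 5km are affected in the same direction (by one third under the decay assumed above).

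Loss of detection is possible but conditional. At 1,200 per group the area DiD has 22% power for 3 points confined to under 1km with a 20% share, 59% under exponential decay and 85% under linear decline. These figures rest on SD 8.7, independent waves, no clustering and assumed distributions of distance. Correlation within persons would raise them. Clustering by practice would lower them (design effect 1 + 99·0.01 = 1.99 at an assumed intraclass correlation of 0.01 with 100 per practice), but that is a separate matter. The choice of the 5km average as primary is not at fault.

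**What to change.** Keep the 5km area-based DiD as the primary analysis. Fit the secondary distance analysis on all participants in one model with distance-band-by-wave (or distance-by-wave) terms and unexposed residents as the reference. Report the nearest band versus unexposed as a pre-specified secondary contrast, and take the within-exposed gradient from the same model. Choose and justify the band limits in the per-wave analysis protocol, with the expected number of participants per band; under 1km is one option, as the compensation boundary.

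Nothing new has to be collected: individual distance and the unexposed sample are already planned, and the change is one model specification. There are two modest drawbacks. The near-band contrast is less precise than the primary (SE 0.870 against 0.502 in the 20% case). Unexposed practices are matched on practice population profile rather than on the characteristics of near-route residents, so the model should adjust for individual baseline characteristics.

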### Sampling and eligibility

We will use a nested sampling design, recruiting general practices and then recruiting participants from those practice populations. A review of GP patient lists by the Office for National Statistics found them to be a reliable population register [45], making this sampling approach broadly equivalent to a traditional address-based sampling approach.

To define “exposed” and “unexposed” general practices we will use geocoded practice postcodes and practice boundary files to identify practices with addresses within 5km of the route of HS2, and practices with boundaries wholly outside 5km of the proposed route. We will also calculate the percentage of each practice population living within 5km of the route of HS2 using the mid-2020 population estimates for Lower layer Super Output Areas (a administratively-defined geographical area consisting of between 400 and 1,200 households; equivalent to a resident population of 1,000 to 3,000 people) [46]. We will exclude practices with less than 750 registered patients to ensure it is feasible to recruit sufficient participants; this is in line with the criteria the Office for Health Improvement & Disparities applies to determine whether practices are included in public health surveillance data sets (https://fingertips.phe.org.uk/profile/general-practice; accessed 17/06/2022). We will also apply an additional criterion for the “unexposed” practices by aiming to recruit those with similar practice population profiles to the “exposed” practices. For each “exposed” practice we will identify a set of “unexposed” practices with similar practice population characteristics using propensity score matching and aim recruit one of the sets to the study. Within “exposed” or “unexposed” practices, adult patients (aged 18 and over) whose registered residential address falls within the “exposed” or “unexposed” geographical regions, respectively, will be eligible for participation in the cohort data collection.

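### The power calculation for WEMWBS ignores sampling by practice, so the stated 90% power is not established for the 600-per-group section of route not proceeding as planned

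*Protocol article*

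**What the plan says.** The sample size reasoning is in the protocol article under Analysis plans, Cohort data. Its inputs are:

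- Error rates: "We considered the sample sizes needed for 90% power based on a 0.05 significance level for a two-sided test".
- Variability: "Data from 2011 estimated the mean WEMWBS for adults in England as 51.6 (standard deviation 8.7".
- Target: the number "is required to detect a minimally important difference of 3 points in the WEMWBS between intervention (n = 178) and control (n = 178) groups".
- Result for the cross-sectional comparison: "a sample size of 178 per group (356 in total for each HS2 Phase) is required to detect" that difference.
- Step to DiD: "sample size requirements for tests of interactions are four times those required to test a main effect of the same size", which gives 356 responses per group at each of two time points.

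Two conclusions follow. On the cross-sectional comparison: "Our target sample sizes far exceed this". On the DiD, with 1,200 per group per Phase and 600 per group for the section not proceeding as planned: "the study will be well-powered to detect a meaningful difference in the primary outcome using a DiD framework".

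The design is described elsewhere. Sampling and eligibility states: "We will use a nested sampling design, recruiting general practices and then recruiting participants from those practice populations". Table 2 sets a minimum of 100 participants per practice. It gives 12 practices per group for Phase 2a, 6 each for Phase 2b West and East, and 6 for the Phase 2b amended route. The Cohort data section makes the primary exposure definition area-based and analyses the section not proceeding as planned on its own.

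**The concern.** People registered with one practice share a neighbourhood and tend to resemble one another. Because exposure is a property of the area, the exposed-versus-unexposed contrast is largely one between practices, and variation between practices enters its standard error. A calculation that counts respondents as independent leaves this out. It also leaves out the few degrees of freedom available when there are only six practices on each side.

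The segment most exposed to this is the one with the fewest practices. It is also the segment that answers the question added to the study's scope: what happens to wellbeing when plans change late. If the power claim is taken at face value, a null WEMWBS result there could be read as evidence against a 3-point effect when such an effect might well have been missed.

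**Working it through.** **Inputs from the protocol.** SD 8.7 (SD² = 75.69), difference 3, two-sided 0.05, 90% power, m = 100 per practice, K = 6 or 12 practices per group.

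**Inputs assumed, because the protocol gives none.** ICC 0.01 to 0.05; practice autocorrelation between waves (CAC) 0.5 or 0.8; effective within-person correlation r of 0 (nobody retained) or 0.5. Here r is the person-level correlation averaged over retained and replaced participants.

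**1. Reproduce the stated figures.**
- Normal formula: 2 × (1.96 + 1.2816)² × 75.69 / 9 = 176.7. The t-test solution is 177.7, rounded up to 178 (power 90.05%).
- DiD: 4 × 356 = 1,424 responses, or 356 per group per wave.
- Triple difference: 4 × 1,424 = 5,696.

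All three match with a design effect of exactly 1. No clustering term, practice degrees of freedom or within-person correlation enters.

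**2. Margin at 600 per group.** 600/178 = 3.37 cross-sectionally; 600/356 = 1.69 for the DiD. Without clustering, DiD power at 600 per cell is about 99% (SE = √(4 × 75.69/600) = 0.71).

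**3. Cross-sectional comparison with clustering.** Design effect = 1 + 99 × ICC. SE = √(2 × 75.69 × design effect / (K × 100)). Power is from the non-central t on 2K − 2 df. Example with K = 6 and ICC 0.02: SE = √(2 × 75.69 × 2.98/600) = 0.867; 3/0.867 = 3.46; power on 10 df is 88%.

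| ICC | Design effect | 178 becomes (per group) | Power, 6 v 6 | Minimum detectable difference (90% power), 6 v 6 |
|---|---|---|---|---|
| 0.01 | 1.99 | 355 | 97% | 2.6 |
| 0.02 | 2.98 | 531 | 88% | 3.1 |
| 0.03 | 3.97 | 707 | 77% | 3.6 |
| 0.05 | 5.95 | 1,060 | 60% | 4.4 |

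Power for 3 points falls below 90% above an ICC of about 0.018 (0.024 by normal approximation). With 12 v 12 practices it is still 91% at ICC 0.05.

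**4. DiD with the same practices at both waves.** Var = 4 × 75.69 × [(1 − ICC)(1 − r)/(K × 100) + ICC × (1 − CAC)/K]. Example with K = 6, ICC 0.02, CAC 0.5, r = 0: 302.76 × (0.98/600 + 0.01/6) = 0.999; SE = 1.00; 3/1.00 = 3.00; power on 10 df is 77%. With r = 0.5 the SE falls to 0.867 and power rises to 88%.

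| 6 v 6 practices, 10 df | ICC 0.01 | 0.02 | 0.03 | 0.05 |
|---|---|---|---|---|
| CAC 0.5, r = 0 | 88% | 77% | 68% | 54% |
| CAC 0.5, r = 0.5 | 97% | 88% | 77% | 60% |
| CAC 0.8, r = 0 | 94% | 90% | 86% | 78% |
| CAC 0.8, r = 0.5 | 99% | 98% | 95% | 88% |

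The second row equals the cross-sectional result because the two variance formulas coincide at CAC = r = 0.5.

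With 12 v 12 practices and r = 0, the lowest DiD power over the same ICC range is 87% at CAC 0.5 (ICC 0.05) and 98% at CAC 0.8.

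**The case against.** Several points on the other side are sound.

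- **The arithmetic is right for independent respondents.** The fault lies in the assumption, not the sums.
- **The DiD cancels stable practice differences, and the study plans to re-engage the same people.** This stands, and the last row of the DiD table shows how far it can help. But the protocol itself expects loss to follow-up over ten years and replacement with new recruits, so r is uncertain. The cross-sectional comparison gains nothing from it.
- **Propensity score matching of practices and covariate adjustment may lower the residual ICC.** Possible, but the protocol does not quantify it. That is a reason to state an ICC range, not to use zero.
- **The minimally important change is given as 3 to 8 points.** At 4 points, cross-sectional power with 6 v 6 practices is about 99.9/98/95/84%. However, the stated sample sizes are for 3 points, and the claim should be judged on that.
- **The protocol says the models will adjust for sampling.** That concerns the analysis and leaves 178 and 356 unchanged. If the models do account for practice, their standard errors will be larger than those used for the power statement.

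A reader might infer that the whole study is underpowered. The documents do not support that: the Phase 2a and 2b analyses keep about 90% power or more over nearly all of the assumed range.

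A reader might also multiply 5,696 by the full design effect. That figure omits clustering too, but subgroups such as age vary within practices, so the full inflation need not apply. The protocol already concedes that it lacks subgroup power for the section not proceeding as planned.

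Nor is the lack of named practice or practice-by-wave model terms a fault here. The protocol defers such detail to analysis protocols pre-registered for each wave.

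**Conclusion.** The concern holds for one segment and two figures. The requirements of 178 per group and 356 per group per wave describe independent respondents, which is not the design being run. For the section not proceeding as planned, 90% power for 3 points is not established. Cross-sectionally it is met at ICC 0.01 and missed from about 0.018 upwards. For the DiD it may be met or missed, depending on the ICC, the practice autocorrelation and retention.

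It would be too strong to say that this segment is shown to be underpowered, since every clustering input above is assumed. What can be said is that the protocol's assurance rests on a calculation that leaves these inputs out, and that plausible values can take power well below 90%. For Phase 2a, and for Phase 2b with West and East combined, the assurance largely stands.

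**What to change.** Recalculate the cross-sectional and DiD requirements using 6 or 12 practices per group, 100 people per practice, a stated ICC range, a practice autocorrelation, and a within-person correlation that reflects expected retention. For the 600-per-group segment, replace the two general assurances with the resulting power or minimum detectable difference. Add a sentence that 5,696 also assumes independent respondents, and that the inflation depends on whether the subgroup varies within or between practices.

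The pre-registered analysis protocol for each wave is a ready place for this. The cost is recalculation and rewording, with no extra participants. The downside is a less favourable stated power for that segment.
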